#### Child-Pugh Score

The Child-Pugh score is calculated from blood test results, presence of ascites and presence of encephalopathy all of which are recorded on the baseline and follow-up CRFs. The blood test results required are serum albumin ( $\text{mg/dL}$ ), INR and serum bilirubin ( $\text{mg/dL}$ ). Where INR is not available, it will be calculated using prothrombin time:  $INR = PT_{patient}/PT_{control}$ . Serum albumin is recorded in  $\text{g/L}$  on the CRFs and serum bilirubin is recorded in  $\mu\text{mol/L}$  on the CRFs. The following conversions are performed before use in the Child-Pugh score formula:

Serum albumin ( $\text{mg/dL}$ ) =  $100 \times \text{Serum albumin } (\mu\text{mol/L})$

Serum bilirubin ( $\text{mg/dL}$ ) =  $0.01131222 \times \text{Serum bilirubin } (\mu\text{mol/L})$

The five constituent variables are each separately categorised into one of three levels (1, 2, 3) in the following way:

|                                    | Score  |                      |                      |
|------------------------------------|--------|----------------------|----------------------|
|                                    | 1      | 2                    | 3                    |
|                                    |        |                      |                      |
| Serum albumin ( $\text{mg/dL}$ )   | >3.5   | 2.8-3.5              | <2.8                 |
| INR                                | <1.7   | 1.7-2.3              | >2.3                 |
| Serum bilirubin ( $\text{mg/dL}$ ) | <2     | 2-3                  | >3                   |
| Ascites                            | Absent | Slight               | Moderate/Severe      |
| Encephalopathy                     | Absent | Moderate(Stage I-II) | Severe(Stage III-IV) |

The Child-Pugh score is then calculated for each participant by adding the five scored

components:

Child-Pugh Score = Serum albumin score + INR score + Serum bilirubin score  
+ Ascites score + Encephalopathy score.

The minimum possible score is 5 and the maximum possible score is 15.

The Child-Pugh score is then converted into the Child-Pugh grade as follows:

| Child-Pugh Score | Child-Pugh Grade |
|-------------------------|-------------------------|
| 5 to 6                  | A                       |
| 7 to 9                  | B                       |
| 10 to 15                | C                       |

*Time to eradication of varices (VBL participants only)*

The date that varices are eradicated is captured on the follow-up CRF. The time till eradication is calculated by taking the difference between date of randomisation and date of eradication.

*Alcohol Consumption*

If the answer to "Does the participant drink alcohol?" is "no" then the response to "On average, how many units of alcohol has the participant consumed per week over the last 12 weeks?" will be by default missing. In this case, the missing value is replaced with 0.

*Coffee Consumption*

If the answer to "Does the participant drink coffee?" is "no" then the response to "On average, how many cups of coffee does the participant drink per day?" will be by default missing. In this case, the missing value is replaced with 0.

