##### MELD Score

The MELD score is calculated via a formula involving serum creatinine (mg/dL), serum bilirubin (mg/dL) and INR which are all components of standard care blood test results. Where INR is

not available, it will be calculated using prothrombin time:  $INR = PT_{patient}/PT_{control}$ . The data will be collected on the baseline and follow-up CRFs. Serum creatinine and serum bilirubin are recorded in  $\mu\text{mol/L}$  on the CRFs. The following conversion is used to obtain values for these measures in  $\text{mg/dL}$ :

Serum creatinine ( $\text{mg/dL}$ ) =  $0.01131222 \times \text{Serum creatinine } (\mu\text{mol/L})$

Serum bilirubin ( $\text{mg/dL}$ ) =  $0.01131222 \times \text{Serum bilirubin } (\mu\text{mol/L})$

These values can then be used directly in the MELD score formula as follows:

MELD Score =  $10 \times [0.957 \times \ln(\max(1, \min(\text{serum creatinine } (\text{mg/dL}), 4)))$   
 $+ 0.378 \times \ln(\max(1, \text{serum bilirubin } (\text{mg/dL})))$   
 $+ 1.120 \times \ln(\max(1, INR)) + 0.643]$

Where the  $\ln()$  function takes the natural logarithm, the  $\max(x, y)$  function takes the larger of the values  $x$  and  $y$  and the  $\min(x, y)$  function takes the smaller of the values  $x$  and  $y$ . The MELD score should then be rounded to the nearest integer.

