## **9.7. Analysis methods – exploratory outcomes and analyses**

Any data that do not form a pre-specified outcome will be presented using simple summary statistics by intervention group (i.e. numbers and percentages for binary data and means (or medians) and standard deviations (or inter-quartile ranges) for continuous normal (or non-normal) data).

Outcomes related to treatment will be presented for the subset of participants that crossed over during the trial. The results will be compared alongside outcomes for participants that did not cross over.

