### **9.9. Planned subgroup analyses**

Interpretation of subgroup analysis will be treated with caution (output will be treated as exploratory rather than definitive). Analysis will be limited to the primary outcome only and the subgroups will be formed around the same variables used in the minimisation algorithm. Tests for statistical heterogeneity will be performed prior to any examination of effect estimates within subgroups. The effects of these subgroups will be examined by including a treatment group by subgroups interaction parameter in the final regression model. P-values for the interactions will be presented for these and interpreted with appropriate caution due to the reduced power. Analysis of primary outcome will be performed and reported within each subgroup in the same fashion as the primary analysis as described in section 9.5. A template for reporting this analyses is given in the final report template.

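### The back-up INR in the MELD and Child-Pugh derivations is a plain prothrombin-time ratio, which equals INR only if the reagent's ISI is 1, so some descriptive severity scores may be shifted (minor)

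*SAP*

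**What the plan says.** SAP section 9.4, under Other Measures, derives MELD and Child-Pugh from baseline and follow-up CRF data. Both derivations contain the same fallback for INR. The Child-Pugh text reads: "Where INR is not available, it will be calculated using prothrombin time". The MELD text says that an INR that is "not available, it will be calculated using prothrombin time". In both places the formula is the patient's prothrombin time over the control prothrombin time, with no exponent. ISI is not mentioned anywhere in the SAP: it is neither collected nor stated to be taken as 1.

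The resulting value is then used exactly like a laboratory INR:

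- In MELD it enters as 10 × 1.120 × ln(max(1, INR)), after which "The MELD score should then be rounded to the nearest integer".
- In Child-Pugh it scores 1 below 1.7, 2 from 1.7 to 2.3, and 3 above 2.3.

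On how such variables are used, section 9.7 says: "Any data that do not form a pre-specified outcome will be presented using simple summary statistics by intervention group". For subgroup analyses, section 9.9 says that "the subgroups will be formed around the same variables used in the minimisation algorithm", and section 4.6 does not list MELD or Child-Pugh among those variables.

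**The concern.** INR exists to put prothrombin times from different reagents on a common scale. By definition it is (PT_patient / PT_control)^ISI. The SAP's fallback omits the exponent, calls the plain ratio INR, and pools it with laboratory-reported INRs in one variable. The MELD coefficient and the Child-Pugh cut-offs are stated for INR, not for an unstandardised ratio.

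Section 4.1 plans for approximately 66 Trusts/Health Boards, so an ISI of exactly 1 throughout should not be assumed without saying so. Where it is not 1, the substituted INR is off by an amount that depends on the local reagent and grows with the ratio. At stake is the accuracy of the reported severity of liver disease at baseline and follow-up for participants whose INR was not reported. The formula will be programmed as written unless it is corrected.

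**Working it through.** The SAP states no numerical result on this point, so there is no figure of the plan to reproduce. The check compares its formula with the definition of INR.

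**Inputs from SAP section 9.4.** Fallback INR = R, where R = PT_patient / PT_control. INR weight in MELD: 10 × 1.120 = 11.2 points per unit of ln(INR), with INR floored at 1 and the score rounded to an integer. Child-Pugh INR cut-offs: 1.7 and 2.3.

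**Assumed input.** The SAP gives no ISI. The range 0.9 to 2.0 is an assumption.

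**Step 1: MELD.** Correct minus planned score, before rounding, is

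11.2 × [ln(max(1, R^ISI)) − ln(max(1, R))],

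which for R > 1 is 11.2 × (ISI − 1) × ln R, and for R ≤ 1 is zero. The creatinine and bilirubin terms are added separately and cancel. At R = 1.7, ln R = 0.5306 and 11.2 × 0.5306 = 5.94, so the difference is 5.94 × (ISI − 1).

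**Step 2: Child-Pugh.** The correct INR reaches a cut-off c at R = c^(1/ISI). The planned rule uses R = c whatever the reagent.

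| ISI (assumed) | Correct INR at R = 1.7 | MELD at R = 1.7, correct − planned | R at which INR = 1.7 | R at which INR = 2.3 |
|---|---|---|---|---|
| 0.9 | 1.61 | −0.59 | 1.80 | 2.52 |
| 1.0 | 1.70 | 0 | 1.70 | 2.30 |
| 1.2 | 1.89 | +1.19 | 1.56 | 2.00 |
| 1.5 | 2.22 | +2.97 | 1.42 | 1.74 |
| 2.0 | 2.89 | +5.94 | 1.30 | 1.52 |

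A positive MELD difference means that the planned score is too low.

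**Step 3: an example that changes a grade.** With R = 1.6 and ISI 1.2, the correct INR is 1.6^1.2 = 1.76. The INR component should be 2, and the plan gives 1. A participant with a planned total of 6 should then total 7, which is grade B rather than grade A in the SAP's own table.

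**Step 4: examples where little or nothing changes.** With R = 1.1 and ISI 1.2, the MELD difference is 11.2 × 0.2 × ln(1.1) = 0.21 points, which rounding may absorb. With R = 1.4 and ISI 1.2, the correct INR is 1.50, so the Child-Pugh component stays at 1. With R at or below 1, neither score changes at any ISI in the range.

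**Step 5: where the scores are used.** Neither score is the primary outcome (4.3), a listed secondary outcome (4.4), a minimisation factor (4.6), a named adjustment covariate (9.1), a subgroup variable (9.9) or a named element of a sensitivity analysis (9.10).

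**The case against.** The strongest objection is that this does not matter to the trial's result. That stands. The scores sit under Other Measures, and their visible use is descriptive: baseline summaries without tests or intervals (6.2) and simple summaries by group (9.7). A reader might infer that the error biases the comparison of carvedilol with band ligation. The documents do not support that, because no section names either score as an input to a treatment-effect model.

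A second objection is that the fallback may rarely be used, since section 9.4 lists INR among the components of standard care blood results. This also stands. The SAP does not say how many participants will lack an INR, so the total effect cannot be calculated.

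Third, a reader might infer that every MELD and Child-Pugh score built on a substituted INR is wrong wherever ISI differs from 1. That goes too far. It is true of the substituted INR unless the ratio is 1. MELD, however, floors INR at 1 and rounds, and Child-Pugh moves only if a cut-off is crossed. Nor is there one direction of error: it reverses when ISI is below 1.

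Fourth, all ISI values here are assumed, and the largest MELD errors pair a high ISI with a ratio of 1.7 that the SAP does not show to be typical. This is fair, and the figures are illustrations rather than estimates.

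Finally, setting all scores without a known ISI to missing would discard usable severity data. That is a reason for a milder remedy, not for leaving the formula as it stands.

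A text-extraction fault is an unlikely explanation. The formula appears identically in two places, and the exponent in the BMI formula of the same section survived.

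**Conclusion.** The formula is wrong as written, with minor consequences. In both derivations the back-up INR is a plain prothrombin-time ratio, which equals INR only if the reagent's ISI is 1 or the ratio is 1. Substituted INRs can therefore be wrong. MELD shifts when the change survives the floor at 1 and the rounding, and the Child-Pugh INR component shifts when the change crosses 1.7 or 2.3.

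With ISI assumed between 0.9 and 2.0, the unrounded MELD error at a ratio of 1.7 runs from 0.6 points too high to 5.9 too low, and is 1.2 too low at ISI 1.2. The number of participants affected is unknown and is limited to those without a reported INR. The harm is confined to descriptive severity data; no planned treatment comparison is touched. The conclusion is separate from any question about the creatinine, bilirubin or albumin unit conversions in the same section.

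**What to change.** In both the MELD and the Child-Pugh derivations, replace the fallback with INR = (PT_patient / PT_control)^ISI, using the ISI of the reagent behind that sample wherever the laboratory can supply it.

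Where the ISI cannot be obtained, do not pool the plain ratio with measured INRs as if the two were equivalent. Flag the scores concerned, report how many there are by group, and tabulate MELD and Child-Pugh with and without them. This keeps the data and lets the reader see whether the substitution matters.

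The cost is a wording change in two places, an ISI query to those sites that report a prothrombin time without an INR, and one extra summary. The primary and secondary analyses are unchanged.

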## **9.5. Analysis methods – primary outcome(s)**

The primary outcome measure of the study is variceal bleeding within the first year after randomisation. This outcome is a binary outcome (i.e. yes/no) and all recruited participants will feature in the primary analysis population. The number and percentage of participants experiencing variceal bleeding within 1 year of randomisation will be reported by treatment group. An adjusted risk ratio and 95% confidence interval will be estimated from a log-binomial model. Risk difference will also be reported. See section 9.1 for covariate adjustment and model convergence. A template for reporting the primary outcome is given in the final report template.

## **9.6. Analysis methods – secondary outcomes**

The secondary outcomes for the trial include continuous, categorical and time-to-event data

items. The analysis population for these outcomes will be restricted to those participants who have reached and provided data for the time point of interest.

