### 5.3. Analysis populations

All primary analyses (primary and secondary outcomes including safety outcomes) will be by intention-to-treat (ITT). Participants will be analysed in the intervention group to which they were randomised, and all participants shall be included whether or not they received the allocated intervention. The analysis population for the four week safety form will comprise only those patients randomised to carvedilol. This is to avoid any potential bias in the analysis.

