## **5.5. Handling protocol deviations and violations**

A protocol deviation/violation is defined as a failure to adhere to the protocol such as errors in applying the inclusion/exclusion criteria, the incorrect intervention being given, incorrect data being collected or measured, follow-up visits outside the visit window or missed follow-up visits. We will apply a strict definition of the ITT principle and will include all participants as per the ITT population described in section 5.3 in the analysis in some form regardless of deviation from the protocol. This includes participants who were randomised but later found to violate the inclusion or exclusion criteria. This does not include those participants who have specifically withdrawn consent for the use of their data in the first instance; however these outcomes will be explored as per other missing responses.

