### 9.3. Handling missing data

In the first instance, analysis will be completed on received data only with every effort made to follow-up participants even after protocol violation to minimise any potential for bias. For the primary outcome, a participant will be assumed to not have experienced variceal bleeding unless there is evidence to suggest otherwise. Therefore, there will be no missing data in this outcome for the primary analysis. However, sensitivity analysis will be performed on the primary outcome measure. See section 9.10 for further details.

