#### **Secondary outcome measures**

##### *Time to first variceal bleed*

Variceal bleeding events are identified as adverse events on the 6 month and 12 month follow-up forms. If a participant has at least one episode of variceal bleeding (including banding-related bleeding) indicated on either of these follow-up forms then they have “experienced variceal bleeding”. Participants which do not fulfil this criteria for experiencing variceal bleeding will be termed “free from variceal bleeding”.

If a participant is termed as having “experienced variceal bleeding” then their time until bleeding will be defined as the number of days from the date of randomisation till the date of onset for the first variceal bleed occurring.

Participants who are termed as “free from variceal bleeding” and who were last known to be

bleeding-free prior to the 12-month follow-up time-point will be censored in the analysis. The time to censoring will be the number of days from the date of randomisation to the date last known to be free from variceal bleeding. This will be determined by the completion date of the most recent trial form received e.g. date of completion on the 12-month follow-up form. If the last known date in the trial is equal to the date of randomisation then the participant will be censored at day 1.

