#### All-cause mortality at one year

Deaths are identified on the SAE form. If a participant has death indicated on an SAE form via the 'death' variable then they will be termed "dead". Participants which do not fulfil this criteria will be termed "alive".

If a participant is "dead" then their time till death will be defined as the number of days from the date of randomisation till the date death. If the time till death is  $\leq 365$  days then the question "All-cause mortality occurred by one year?" is termed "yes". If the time till death is  $> 365$  days then the question "All-cause mortality occurred by one year?" is termed "no".

If a participant is "alive" then their time till censoring will be the number of days from the date of randomisation to the date last known to be alive. This will be determined by the completion date of the most recent trial form received. If the censored time is  $> 365$  then the question "All-cause mortality occurred by one year?" is answered "no". If the censored time  $\leq 365$  days but the follow-up CRF has been completed within the window of assessment (no earlier than 351 days from randomisation) then "All-cause mortality occurred by one year?" is answered "no". If the censored time is  $\leq 365$  and the 12-month follow-up CRF has not been returned within the scheduled window of assessment then there is not complete information regarding mortality within 1 year for this participant. Therefore, the answer to "All-cause mortality occurred by one year?" is considered to be missing.

Liver-related mortality and cardiovascular mortality will be derived in a similar fashion. Deaths of these types will be classified and indicated on the database following review of the SAE information provided by the chief investigator.

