#### *Adverse events relating to treatment*

These events (as listed in section 4.4) will be analysed and reported in the same way as all-cause mortality.

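### SAP section 9.6 limits all secondary outcomes to participants who reached the time point: this contradicts section 9.4 and, for adverse events and complications, would exclude events already recorded

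*SAP*

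**What the plan says.** Section 9.6 first notes that the secondary outcomes are of continuous, categorical and time-to-event type. It then states, with no exception: "The analysis population for these outcomes will be restricted to those participants who have reached and provided data for the time point of interest".

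Other parts of the SAP bear on the same question:

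- **Section 5.3** places primary, secondary and safety outcomes under intention to treat, by allocated group, and adds that "all participants shall be included whether or not they received the allocated intervention". **Section 5.5** says: "We will apply a strict definition of the ITT principle".
- **Section 9.3** says: "In the first instance, analysis will be completed on received data only".
- **Section 9.4, time to first bleed.** A bleed is timed at its onset. Those without a bleed who were last known to be "bleeding-free prior to the 12-month follow-up time-point will be censored in the analysis" therefore stay in.
- **Section 9.4, mortality.** "Deaths are identified on the SAE form", and a death at 365 days or earlier is a yes. Status is missing only for someone not known to have died, last seen by day 365, with no 12-month form in the window.
- **Section 9.4, transplant-free survival.** Transplants also come from the SAE form, and one at 365 days or earlier settles the outcome.
- **Adverse events and complications of cirrhosis.** Section 9.4 has no derivation for either. Section 9.6 says only that they "will be analysed and reported in the same way as all-cause mortality".

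**The concern.** Needing data at the time point is natural for a questionnaire score at 6 or 12 months. It does not suit an outcome that asks whether something happened at any time in the first year. Such an outcome can be settled well before month 12, and the people in whom it is settled early include those most likely to die or withdraw. Requiring them to reach month 12 selects the analysis set on something that happens after randomisation and is related to the outcome, and perhaps to the treatment.

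Two things are at stake. Where sections 9.4 and 9.6 both speak, two programmers could build different datasets from the same plan. Where only section 9.6 speaks, recorded events can drop out of the comparison. Survival, complications and adverse events together form the first secondary objective in section 3. Section 9.10 confines sensitivity analyses to the primary outcome, so no planned analysis would show the loss.

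**Working it through.** **1. The rules side by side.** Take three participants.

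- *Dies in month 5.* Section 9.4 counts a death within one year. Section 9.6, read literally, leaves the participant out because month 12 was never reached.
- *Bleed-free, withdraws in month 7.* Section 9.4 keeps the participant in the time-to-bleed analysis, censored at the date of the last form. Section 9.6 leaves the participant out.
- *New ascites on the six-month form, withdraws in month 8.* Section 9.4 is silent. Section 9.6 leaves the participant out, although the complication is known.

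The first two cases are contradictions. In the third, section 9.6 is the only explicit rule, and it excludes a known event.

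**2. Inputs for the size.** The SAP gives no figure for these outcomes, so every rate below is an assumption. The one plan figure used is 1315 per group (section 4.7), for scale. Its basis reproduces: 12% against 8%, two-sided 5%, 90% power gives 1181 per group, and 2362/0.90 gives 2625 after rounding up, close to the stated 2630. The sample size is not affected by this point.

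**3. Effect on the risk in one arm.** Let p be the true risk, a the proportion of those with the event who leave before month 12, and b the same proportion among those without it.

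Reported risk = p(1 − a) / [p(1 − a) + (1 − p)(1 − b)]

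With p = 0.20 and b = 0.10:

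- a = 0.10: 0.18 / (0.18 + 0.72) = 20.0%
- a = 0.20: 0.16 / (0.16 + 0.72) = 0.16/0.88 = 18.2%
- a = 0.40: 0.12 / (0.12 + 0.72) = 0.12/0.84 = 14.3%

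In an arm of 1315 there would be 0.20 × 1315 = 263 events. The rule excludes 0.20 × 263 ≈ 53 of them in the second case and 0.40 × 263 ≈ 105 in the third.

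**4. Effect on the comparison.** Let the true risk be 20% in both arms, so the true risk ratio is 1.00, and let a = 0.10 in one arm.

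- a = 0.20 in the other arm: 0.182/0.200 = 0.91
- a = 0.40 in the other arm: 0.143/0.200 = 0.71

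The arm in which the event more often leads to exit looks safer than it is.

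**5. A wider range.** Assume a 10% risk in completers, a risk q of 20% to 60% in early leavers, all recorded before exit, and an early-exit proportion e of 10% to 25%. True risk = (1 − e) × 0.10 + e × q.

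- Lowest: 0.90 × 0.10 + 0.10 × 0.20 = 11%. Share of events excluded: 0.02/0.11 = 18%, about 26 events in 1315.
- Highest: 0.75 × 0.10 + 0.25 × 0.60 = 22.5%. Share of events excluded: 0.15/0.225 = 67%, about 197 events in 1315.

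The reported risk is 10% throughout.

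**The case against.** **The detailed rules in section 9.4 govern, and section 9.6 can be read to fit them.** On this reading, having reached the time point means that it has fallen due, which matters at interim analyses, and having provided data means that the outcome can be classified. By the final analysis all participants should be past one year (section 4.11). Much of this stands. From the literal wording a reader might infer that the one-year mortality analysis would contain no deaths. The SAP does not support that, because section 9.4 counts every death on an SAE form by day 365, and recorded bleeds and transplants are kept too. For these outcomes the fault is a contradiction and not a settled loss. But the reconciling reading is nowhere written, and section 9.6 names time-to-event items expressly.

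**Treating adverse events and complications like all-cause mortality may carry over its counting rule.** This is possible. However, the phrase follows a paragraph on the log-binomial model, risk ratio and risk difference, so it most naturally refers to method. Where section 9.4 extends the mortality derivation, it does so in words, and only to liver-related and cardiovascular deaths.

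**An available-case analysis by allocated group is compatible with ITT as the SAP uses the term.** Largely so. Section 5.3 is mainly about allocation regardless of treatment received, section 5.5 speaks of inclusion in some form, and section 9.3 starts from received data. A reader might infer that the plan abandons ITT, which is too strong. Yet a completed six-month form is received data, and section 9.6 adds a further condition that would exclude it.

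**Harms are reported elsewhere.** Section 9.8 presents any adverse events, SAEs and SUSARs by arm, outside the section 9.6 restriction. A reader might infer that the plan hides harm, and it does not. What is exposed is the adjusted comparison of the named secondary outcomes.

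**The rates are assumed.** They are. The figures show direction and possible size and are not a forecast.

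**Conclusion.** The point holds in two parts. For time to first bleed, mortality and transplant-free survival, sections 9.4 and 9.6 contradict each other and must be reconciled; section 9.6 also sits badly with section 5.3. For treatment-related adverse events and complications of cirrhosis, the only explicit population rule excludes events already recorded in participants who later die or withdraw.

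That exclusion understates the risk whenever people with the event leave more often than people without it. It biases the comparison if exit after an event differs by arm. The illustration of 20% reported as 18.2% or 14.3% rests on the assumed exit proportions and on the sentence being applied as written. The primary outcome is untouched, because section 9.5 includes all recruited participants. For EQ-5D-5L the restriction is an ordinary available-case analysis.

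**What to change.** Limit the section 9.6 sentence to EQ-5D-5L. For all other secondary outcomes, state that:

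- all randomised participants are included in their allocated group;
- any event recorded as occurring within 365 days counts, whatever happens to later follow-up;
- event-free participants with incomplete follow-up are censored for time to first bleed and treated as missing for the binary outcomes, as in section 9.4. Censoring cannot be used for the binary outcomes, since the log-binomial models have no place for it.

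Add to section 9.4 a derivation that applies this rule by name to the adverse events and complications listed in section 4.4. The SAP does not say whether onset dates are collected for all of these, so the derivation should state which date is used when there is none.

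One limit should be acknowledged. Keeping all known events while setting lost non-events to missing overstates risk somewhat: with p = 0.20 and 10% of non-events lost, 0.20/(0.20 + 0.72) = 21.7%. Section 9.4 already accepts this for mortality.

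The cost is SAP wording and minor programming, with no change to the models or the sample size.
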